## Abstract

Background/Objectives: The use of coercive measures (CMs) and security technologies (STs) in mental healthcare continues to raise ethical and practical concerns, affecting both patient and staff well-being. Mental health nurses (MHNs) and nursing students (NSs) play a key role in the decision-making process regarding these interventions. However, their attitudes, particularly toward STs, remain underexplored in Italy. This study protocol aims to introduce a new conceptual framework and investigate Italian MHNs’ and NSs’ attitudes toward CMs and STs in mental health settings. Additionally, it will explore the influence of sociodemographic and psychological factors, including stress, anxiety, depression, stigma, and humanization on these attitudes. Methods: The research will be conducted in two phases. Phase 1 involves a national survey of a convenience sample of MHNs and NSs to assess their attitudes and related factors. Phase 2 includes qualitative interviews with a purposive sample of MHNs and NSs to explore participants’ perspectives on STs in more depth. Quantitative data will be analyzed using descriptive and inferential statistics, while qualitative data will be examined through thematic analysis. Conclusions: This study protocol seeks to enhance our understanding of MHNs’ and NSs’ attitudes toward the use of CMs and STs in mental health settings, identifying key factors influencing these attitudes. The findings aim to inform policy development, education programs, and clinical practices in both the Italian and international panoramas. Additionally, the proposed conceptual framework could guide future research in this field.

## 1. Introduction

The primary aim of psychiatric care is ‘to keep patients and others safe’ [1], highlighting the value of safety in mental health [2]. However, mental health settings face several challenges that can compromise safety [3]. These challenges include patient falls [4], adverse reactions to therapeutic interventions [5], and difficult patient behaviors, such as absconding [6]. Violence remains a critical issue, with a significant number of psychiatric inpatients exhibiting violent behavior [7], engaging in self-harm, or revealing suicidal tendencies [8]. Furthermore, up to 85% of mental health staff report experiencing assaults [9], which can lead to physical injuries [10] and psychological consequences [11].

### 1.1. Coercive Measures

These safety challenges are potential antecedents of coercion [12], precipitating the use of coercive measures (CMs) [13,14]. CMs are defined as ‘a medical measure carried out against the patient’s self-determined wishes or in spite of opposition’ [15]. Formal CMs include involuntary admission, observation, seclusion, forced medication, and restraint [12], while informal CMs encompass practices such as persuasion, manipulation, and threat [16].

Despite their common use, CMs raise significant concerns [12]. Patients subject to CMs may experience fear, anger, trauma [17,18], physical injury, or even death [19]. Staff implementing CMs can face the risk of physical harm [20], frustration, guilt, and ethical dilemmas [21,22,23]. Additionally, CMs can damage therapeutic relationships, infringe on patients’ rights, and reinforce stigma [12,24]. Although policies such as the Safewards Model [25] have shown promise to reduce CMs, they remain prevalent in contemporary mental health practices [26], and mental health staff still consider CMs necessary for maintaining safety [27,28].

### 1.2. Security Technologies

In light of the challenges and ethical concerns surrounding CMs, there is growing interest in alternative strategies to enhance safety in mental healthcare [29,30]. One emerging solution is the use of security technologies (STs), such as surveillance cameras, body-worn cameras, personal or fixed alarms, and metal detectors [31,32,33,34]. These technologies can enhance safety by enabling remote patient monitoring [31], facilitating rapid incident response [35], and preventing the introduction of dangerous items [32]. International guidelines support the use of STs such as surveillance cameras and alarms to mitigate suicide and violence in mental health [36,37], while in Italy, psychiatric forensic facilities already integrate them [38] following national policies [39,40].

However, research on the use of STs in mental health settings is still emerging [31,33,34]. While some studies highlight their values in enhancing safety and well-being [32,41], others identify potential risks, including increased property damage and violence [42,43]. Ethical concerns related to patient consent, privacy, and dignity also complicate their adoption [31,44,45].

### 1.3. The Role of Mental Health Nurses and Nursing Students

Mental health nurses (MHNs) are crucial in ensuring safety in psychiatry, also using CMs [46]. Therefore, extensive research has reviewed MHNs’ attitudes toward CMs [21,23,29], highlighting mixed findings and the need for further studies [23,27,29]. For instance, MHNs’ attitudes toward CMs are underexplored in Italy [47], with studies predominantly focused on general attitudes toward mental illness [48] and informal coercion [49]. Similarly, while international research is beginning to explore MHNs’ perspectives on certain STs such as body cameras [33,44,45], exploration of the attitudes towards an extensive range of STs is still lacking.

Nursing students (NSs) also participate in psychiatric care during their internship [50,51]. They actively witness, assist, and implement CMs [52,53], and can develop favorable attitudes toward them [53,54,55]. Furthermore, their perceptions could strongly predict the application of CMs [56]. However, despite their involvement, NSs’ attitudes toward both CMs and STs are underexplored.

### 1.4. Conceptual Framework

The conceptual framework guiding this research integrates Johansen’s [57] and Moylan’s [58] decision-making models, enriched by key theoretical insights from the literature. Johansen’s model highlights how education, experience, values, knowledge, and stress influence decision-making in nursing practice [57]. Moylan’s model focuses on how MHNs navigate among perceived risks, available information, and personal values when selecting CMs in response to patient aggression [58]. Both models are pertinent to MHNs, who are described as ‘leaders during the application of restrictive practices in psychiatry’ [59], with substantial responsibility for initiating CMs [27].

This framework is further supported by the Theory of Planned Behaviour [60] and the Normative-Affective Decision-Making Theory [61], which highlights how beliefs, social norms, and emotional factors shape attitudes and behaviors. This aligns with existing research suggesting that both personal and normative factors have a strong influence on attitudes toward the use of CMs and STs [23,62,63].

Based on these models and the existing literature, the proposed framework (see Figure 1) suggests that MHNs’ and NSs’ attitudes toward CMs and STs are shaped by three main categories of factors: individual, psychological, and contextual factors.

#### 1.4.1. Individual Factors

Staff characteristics: Evidence suggests that sociodemographic characteristics may influence attitudes and behaviors toward the use of CMs. Male MHNs are more likely to use CMs compared to females [13,14,64,65]. Shifts involving male MHNs have been associated with increased use of CMs [63]. Male NSs also express greater confidence in applying CMs [54,66]. However, some research suggests that female MHNs may exhibit more favorable attitudes toward CMs [65], with their presence linked to higher rates of seclusion [67]. Age is another important factor: younger MHNs tend to be more supportive of CMs [68], while older MHNs often express ethical concerns [69]. Additionally, MHNs’ ethnicity has been identified as influencing CMs’ use [70].

Experience and Training: The relationship between experience, training, and attitudes toward CMs is complex, with research providing mixed results. Some studies indicate that higher education correlates with increased CMs use [63,64], while others show that more educated MHNs are less supportive [14,67]. Work experience also plays a significant role. More experienced MHNs often resort to CMs less frequently [67], and hold critical views on their use [22,66]. In contrast, some studies report that experienced MHNs continue using CMs consistently [68,71,72]. Less experienced MHNs may view CMs as beneficial interventions [73], and adopt more restrictive approaches [65,67,73]. Additionally, feelings of being underskilled [74] or inexperienced in mental health nursing [64,75] are associated with higher reliance on CMs.

#### 1.4.2. Psychological Factors

Emotions and Feelings: Emotional states can influence decisions to use CMs in psychiatric settings. Emotions such as anger, fear, stress, and anxiety can increase the likelihood of MHNs resorting to CMs [28,46,68]. Stress and anxiety can undermine MHNs’ confidence in managing aggression, increasing their reliance on CMs [22]. NSs show similar tendencies, supporting the use of CMs when experiencing anxiety and fear [76]. Additionally, team dynamics and interpersonal conflicts among nursing staff are linked to higher CM use [25,77]. Conversely, positive emotional traits such as empathy are associated with a reduced likelihood of employing CMs [78].

Beliefs and Values: Beliefs and values can shape MHNs’ attitudes toward CMs. A greater perception of risk is typically associated with increased use of CMs [29,79]. Similar trends are observed among NSs [76]. Ward culture and norms further influence the acceptance or rejection of CMs [72,73,75,80], leading to variations in CM use across units and countries [13,64]. Familiarity with CMs also predicts more favorable attitudes among MHNs and NSs [54,55,66,76,81]. Additionally, stigma toward mental illness, common among MHNs and NSs [82,83], can influence the approval of CMs [84].

#### 1.4.3. Contextual Factors

Ward characteristics: The wards’ physical environment and operational structure can influence the use of CMs [80]. Working in open versus closed units, or acute versus chronic settings, shapes MHNs’ attitudes toward CMs [64,65,71,77]. Heavy workloads and staffing shortages increase the likelihood of using CMs, as MHNs may lack sufficient resources to manage incidents effectively [79,85]. For instance, shifts with less experienced staff are linked to higher CMs use [64]. Additionally, poor leadership, inadequate safety protocols, and organizational dysfunction contribute to increased reliance on CMs [74,77].

Patient characteristics: Patient-specific factors, such as diagnosis severity and type, are key determinants in decisions to implement CMs [13,85,86]. Patients exhibiting aggressive behaviors or refusing treatment are more likely to experience CMs [14,62,63,65]. Sociodemographic factors also play a role: patient sex [13,71,86,87], age [13], ethnicity [13,87], and marital status [87] can influence CMs use. Additionally, patients admitted involuntarily are more likely to be subjected to CMs compared to voluntary admissions [13].

## 2. Materials and Methods

### 2.1. Research Hypothesis

Based on the literature and the conceptual framework developed, the following research hypotheses were formulated:(1)Attitudes toward coercive measures and security technologies in psychiatric settings differ between mental health nurses and nursing students.(2)In mental health nurses and nursing students, attitudes toward coercive measures and security technologies in psychiatric settings vary depending on the specific type of strategy considered.(3)In mental health nurses and nursing students, attitudes toward coercive measures and security technologies in psychiatric settings are influenced by sociodemographic and psychological variables, including levels of depression, anxiety, stress, stigma toward mental illness, and humanization of care.

### 2.2. Objectives

The primary aims of the research are as follows:Assess the attitudes of mental health nurses and nursing students toward coercive measures and security technologies in Italian psychiatric settings.Investigate the associations between these attitudes and sociodemographic and psychological variables in mental health nurses and nursing students.

The secondary aim is as follows:Qualitatively explore the perspectives of mental health nurses and nursing students regarding the appropriateness of security technologies in mental health settings.

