#### 2.5.4. Data Collection and Questionnaire

Data will be collected using an online self-report questionnaire hosted on Google Forms ©, designed according to best practices in survey methodology [89]. Online surveys are particularly suitable for research on sensitive topics, as they promote honest responses, reduce social desirability bias, and enhance data reliability [107].

The questionnaire consists of seven sections with a total of 90 closed-ended items. The first section gathers sociodemographic information, the second collects professional or academic data (distinguishing between MHNs and NSs), and the third evaluates attitudes toward CMs and STs. The subsequent sections include three validated Italian instruments to measure psychological variables, and the final section assesses participants’ willingness to engage in the qualitative study.

Due to the lack of existing instruments to evaluate MHNs’ and NSs’ attitudes towards CMs and STs, the third section was developed by the authors. The method employed mirrors the approach used by Bowers and colleagues [108] in designing a survey to explore safety procedures and measures used in psychiatric units. The development process involved establishing the theoretical framework, performing a literature review, and conducting a focus group involving the authors and five experts: two mental health chief nurses, two nursing professors, and a statistician. To ensure clarity and relevance, content and face validity testing was conducted using established methodologies [109,110]. The content validity ratio (CVR) ranged from 0.60 to 1, exceeding the minimum threshold of 0.49 [111]. The item-level content validity index (I-CVI) ranged from 0.80 to 1, surpassing the cut-off of 0.70 [112]. Additionally, the scale-level content validity index (S-CVI/Ave) was 0.90, above the recommended threshold of 0.80 [109]. Evaluation of face validity further confirmed that the questions were clear, relevant, and applicable to the study’s objectives. Consequently, the items were deemed valid for administration.

The entire questionnaire was then tested on ten participants from each population to evaluate completion times, which ranged from 16 to 30 min. This length aligns with recommendations for maintaining participant engagement in online surveys [113]. The completion times are also consistent with the literature on web survey responses, where participants typically spend between one and ten seconds per question [114].

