The questionnaire will be structured as follows:1.Sociodemographic variables: In this six-item section, participants will provide demographic information including sex, age, marital status, ethnicity, and spiritual beliefs. They will also indicate their current role (MHN or NS) to ensure they receive the appropriate subsequent questions. The anticipated completion time is two minutes.2a.Questions for MHNs: In this 14-item section, MHNs only will answer questions about their working role (i.e., clinical or chief nurse), educational level (e.g., bachelor’s or master’s degree), education in mental health nursing (i.e., yes or no), years of work experience, years of work experience in mental health, geographical region, work setting (i.e., acute, community, residential), contract type (i.e., permanent or fixed-term), work schedule (i.e., full-time or part-time), and work pattern (i.e., shift or daytime). They will also assess their perceived workplace safety, job satisfaction, intention to change work settings, and inclination to leave the profession, using a 5-point Likert scale (1 = not at all; 5 = very). The anticipated completion time is five minutes.2b.Questions for NSs: In this nine-item section, NSs only will be asked about the geographical region where their program is located, academic status (i.e., full-time or part-time student), year of enrolment, education in mental health nursing (i.e., yes or no), internship pattern (i.e., shift or daytime), and hours spent in mental health internships. Additionally, they will evaluate their academic satisfaction, intention to leave the program, and interest in working in the mental health field using a 5-point Likert scale (1 = not at all; 5 = very). The anticipated completion time is four minutes.3.Attitudes towards CMs and STs: In this eight-item section, participants will assess the appropriateness of CMs and STs commonly used in psychiatry according to the literature, including physical restraints, pharmacological restraints, locked ward doors, video surveillance systems, body-worn cameras, fixed alarms, portable alarms, and metal detectors. Responses will be collected using a 5-point Likert scale (1 = not at all appropriate; 5 = very appropriate). The anticipated completion time is four minutes.4.Depression Anxiety Stress Scale (DASS-21): This 21-item scale measures levels of depression, anxiety, and stress [115]. Participants will report the frequency of symptoms experienced over the past week on a 4-point Likert scale (0 = never; 3 = almost always). The total score for each dimension will be calculated. Internal consistency values are α = 0.82 for depression; α = 0.74 for anxiety; α = 0.85 for stress. The anticipated completion time is seven minutes.5.Opening Minds Stigma Scale for Healthcare Providers (OMS–HC): This 12-item scale measures stigma towards mental illnesses, focusing on attitudes towards people with mental illnesses and disclosure of mental illness [116]. Participants will indicate their agreement with each statement using a 5-point Likert scale (0 = strongly disagree; 4 = strongly agree). Higher scores indicate greater levels of stigma. Internal consistency values are α = 0.74 for stigma towards people with mental illness and α = 0.86 for stigma towards disclosure. The anticipated completion time is five minutes.6.Healthcare Professional Humanization Scale (HUMAS-I): This 19-item scale evaluates the humanization of care across five dimensions: affection, self-efficacy, emotional understanding, optimistic disposition, and sociability [117]. Participants will rate the frequency of their experiences using a 5-point Likert scale (1 = never; 5 = always). Aggregate scores will be calculated for each dimension and the overall scale. Internal consistency values are as follows: α = 0.87 for affection; α = 0.82 for self-efficacy; α = 0.81 for emotional understanding; α = 0.82 for optimistic disposition; α = 0.70 for sociability. The anticipated completion time is seven minutes.7.Willingness to participate in an interview: A dichotomous question (yes/no) will determine participants’ willingness to engage in the interview.

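### Nurses' work setting is collected and said to shape attitudes toward coercive measures, but H3, Objective 2 and the named confounders omit it, leaving nurses' stress–attitude associations open to confounding by setting

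*Protocol article*

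**What the plan says.** - **Framework (section 1.4).** Attitudes are "shaped by three main categories of factors: individual, psychological, and contextual factors".
- **Contextual factors (section 1.4.3).** "Working in open versus closed units, or acute versus chronic settings, shapes MHNs’ attitudes toward CMs". A separate sentence says "Heavy workloads and staffing shortages increase the likelihood of using CMs"; it concerns use, not attitudes.
- **H3 (section 2.1).** The hypotheses are said to rest on the literature and the framework. H3 states that attitudes "are influenced by sociodemographic and psychological variables, including levels of depression, anxiety, stress, stigma toward mental illness, and humanization of care".
- **Objective 2 (section 2.2), a primary aim.** "Investigate the associations between these attitudes and sociodemographic and psychological variables in mental health nurses and nursing students".
- **Questionnaire (section 2.5.4).** The first section is sociodemographic: sex, age, marital status, ethnicity, spiritual beliefs and current role. By contrast, "the second collects professional or academic data (distinguishing between MHNs and NSs"). For nurses this second section has 14 items, among them "work setting (i.e., acute, community, residential"), shift or daytime work, and years in mental health. For students it has nine items, among them year of enrolment and hours of mental health internship.
- **Analysis (section 2.5.5).** Methods are descriptive and bivariate. Confounders are to be handled by stratification, and the examples given are sociodemographic and psychological factors.

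**The concern.** By the protocol's own account, setting is related to an outcome of the survey, and setting is recorded for every nurse. It nevertheless falls between the two groups of variables that H3, Objective 2 and the confounder sentence name, because the questionnaire keeps professional data apart from sociodemographic data.

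H3 is worded as influence, not mere co-occurrence. If nurses in acute settings are both more stressed and more approving of restraint, the bivariate correlation between stress and approval will be positive even if stress has no bearing on approval within any setting. The paper would then report a psychological determinant where there is a setting effect, although it holds the variable needed to tell the two apart.

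Experience is in a similar position. The framework places it under individual factors, in a block of its own beside staff characteristics, and the questionnaire collects it in the professional section.

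**Working it through.** **1. The plan's own figure.** Section 2.5.3 gives n = 1.96² × 0.5 × 0.5 / 0.05² = 384.16, that is 384 per population. It reproduces. It is used here only to set the scale.

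**2. Where the variables appear.**

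| Variable group | Framework | Collected | H3 and Objective 2 | Named confounder |
|---|---|---|---|---|
| Sociodemographic | yes | yes | yes | yes |
| Psychological | yes | yes | yes | yes |
| Experience, training | yes (individual) | yes | not named | not named |
| Work setting | yes (contextual) | yes, nurses only | not named | not named |
| Unit openness, staffing, workload, leadership, patient mix | yes (contextual) | no | not named | not named |

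**3. What an omitted setting could do.** The documents give no effect sizes, so the inputs are assumptions:
- a share p of nurses is in acute settings;
- stress and attitude are both higher there by d within-setting SDs;
- there is no stress–attitude link within settings;
- the test is two-sided at 0.05 (section 2.5.5 sets the level but not the sidedness), and attitude is treated as continuous.

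Spurious correlation: r = p(1−p)d² / (1 + p(1−p)d²).

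Rejection probability: with z = atanh(r) × √(n−3) and n = 384, it is Φ(z − 1.96) + Φ(−z − 1.96). The smallest significant |r| is 0.100.

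Example with p = 0.5 and d = 0.5: p(1−p)d² = 0.0625, so r = 0.0625/1.0625 = 0.059. Then z = 0.0589 × √381 = 1.15, and the rejection probability is Φ(−0.81) + Φ(−3.11) = 0.21.

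| d | r, p = 0.5 | significant | r, p = 0.33 | significant |
|---|---|---|---|---|
| 0.3 | 0.02 | 7% | 0.02 | 7% |
| 0.5 | 0.06 | 21% | 0.05 | 18% |
| 0.6 | 0.08 | 37% | 0.07 | 30% |
| 0.8 | 0.14 | 77% | 0.12 | 68% |

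**4. Does adjustment repair it?** This was simulated with three equally frequent settings, one of them shifted on both variables, 384 nurses and 4,000 runs.

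| d | unadjusted | adjusted for setting |
|---|---|---|
| 0.3 | 6.6% | 5.1% |
| 0.5 | 17.5% | 5.2% |
| 0.8 | 68.6% | 4.8% |

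**5. Can the planned stratification carry it?** Setting has 3 levels and work pattern 2. Assume 3 bands for years in mental health. That gives 3 × 2 × 3 = 18 cells, and 384/18 ≈ 21 nurses per cell if they were evenly filled. Adding mental health education (yes or no) gives 36 cells of about 11. This is before any of the sociodemographic or psychological strata that section 2.5.5 already has in mind.

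**The case against.** Several objections have force.

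- **The confounder list is open.** Section 2.5.5 gives its two groups as examples, so setting is unnamed, not excluded. The same section describes all variables and plans ANOVA for comparisons of more than two groups, which a three-level work setting would fit. A reader might infer that setting will not be analyzed at all; the text does not say so. But an open list leaves the choice of adjusters until after the data are seen, and comparing attitudes across settings does not adjust the stress–attitude association.
- **Only half the confounding path is documented.** The setting–attitude link is stated, without a direction. A setting–stress link is plausible but appears nowhere. A reader might infer that the associations are confounded; the documents support only that they are open to it.
- **The reach is limited.** Section 1.4.3 speaks of coercive measures, which are three of the eight attitude items; the other five are security technologies. Students are not asked for a work setting. Workload is tied to the use of coercive measures, so it cannot be cited as a stated driver of attitudes.
- **Testing part of a framework is a scope choice.** Resting hypotheses on a framework does not promise a test of every arm. The mismatch is therefore not a contradiction in itself.
- **The term sociodemographic might be meant broadly.** The questionnaire's sociodemographic section does include current role. Even so, section 2.5.4 separates the two kinds of data, and section 1.4.1 treats sociodemographic characteristics apart from experience and training.
- **A condensed article may leave a full list of adjusters to another document.** That is fair for the full list. It does not cover the wording of a primary objective and a hypothesis, which a fuller plan would inherit.

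**Conclusion.** The concern holds in a limited form. For mental health nurses, and chiefly for the three coercive-measure items, the planned stress– and anxiety–attitude associations are open to confounding by work setting. The protocol itself links setting to attitudes and collects it, but names it in neither H3, Objective 2 nor the confounder sentence.

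The size is unknown. Under the stated assumptions (50% of nurses in acute settings, equal shifts in the same direction, n = 384), the false-positive rate would be about 7% at 0.3 SD, which is close to nominal, and about 77% at 0.8 SD. Nothing in the documents favors either end of that range. What is firm is that adjusting for a variable already collected brings the rate back to about 5% in every case simulated.

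For students the mechanism is different and weaker. Their adjusters rest on the framework's experience and training block, not on setting.

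**What to change.** 1. **Section 2.5.5.** Name the adjusters in advance: for nurses, work setting, work pattern and years in mental health; for students, year of enrolment and mental health internship hours.
2. **Section 2.5.5.** Estimate the psychological–attitude associations by partial correlation or by a linear or ordinal regression model, in place of stratifying on all adjusters.
3. **Sections 2.1 and 2.2.** Extend H3 and Objective 2 to the collected professional and academic variables, or state why they are excluded.
4. **Section 2.8.** State that unit openness, staffing, workload, leadership and patient mix are not measured, so the framework's contextual arm is examined only in part.

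Cost: wording in four sections and one added model per attitude item in each population. The nurse adjusters use about four degrees of freedom (two for setting, one for work pattern, one for years entered linearly) out of 384 participants. No new questionnaire items or participants are needed.
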